| Weight                                     | X         |                | X                                                          |                |                |                |                | X        |                |                |                 | X              |                | X                                    |          | X              |
| Waist circumference                        |           |                | X                                                          |                |                |                |                | X        |                |                |                 | X              |                | X                                    |          | X              |
| 12-lead-ECG E                   | X         |                |                                                            |                |                |                |                |          |                |                |                 |                | X              | X                                    |          |                |
| Diet & exercise counselling F   |           | X G | X                                                          | X              | X              | X              | X              | X        | X              | X              | X G  | X              | X              | X                                    | X        | X              |
| Pregnancy Test H                | X         |                |                                                            |                |                |                |                |          |                |                |                 |                | X              | X                                    |          |                |
| Daily FPG via HBGM I            |           | X              | X                                                          | X              | X              | X              | X              | X        | X              | X              | X               | X              | X              | X                                    | X        | X              |

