| Dispense BI 10773 25 mg O       |           |                |                                                            | X              |                |                |                | X        |                |                |                 |                |                |                                      |          |                |
| Medication compliance                      |           |                | X                                                          |                | X P | X P | X P | X        | X P | X P | X               | X              | X              | X                                    |          |                |
| Trial termination                          |           |                |                                                            |                |                |                |                |          |                |                |                 |                |                |                                      |          | X              |

Proprietary confidential information.

© 2012 Boehringer Ingelheim International GmbH or one or more of its affiliated companies. All rights reserved.

This document may not - in full or in part - be passed on, reproduced, published or otherwise used without prior written permission.

- A. Visits 2, 11 and if required EOT are the only clinic visits where a fasting status is required for labs. Visit 2 to be performed preferably within 1 week of Visit 1. If subjects discontinue the trial after the start of therapy and prior to completion of Visit 13, an end of treatment (EOT) visit should be done as soon as possible and the following will be performed: A physical exam including vitals, an ECG and laboratory assessments (FPG, HbA1c, ~~GA~~ ~~FA~~, Hematology, Chemistry, Lipids, Urine B and hCG). The EOT visit must be performed instead of a scheduled clinic visit for early discontinued subjects in cases where discontinuation occurs during a scheduled clinic visit. Early discontinued subjects should return to the clinic only for follow up Visit 15 (Visit 14 may be skipped). Refer to [Section 6.2.3](#) for details. If feasible, early discontinued subjects should continue with CGM and HBGM until Visit 15.

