| 13:30-14:00 | Repeat measurements of MAP, GFR, ERPF, FF, RBF and RVR (all average of 2 measurements), RAAS mediators, NO, prostanoids, arterial stiffness and markers of sympathetic nervous system activation (heart rate variability and circulating plasma levels of adrenaline/noradrenaline) and other laboratory assessments.                                                                  |

- E. In addition to the required ECG at Visit 1 and Visit 13, additional ECGs should be performed in cases of cardiac symptoms (rhythm disorders or cardiac ischemia).
- F. Subjects will be advised to follow a healthy diet and exercise program based on investigator recommendations during the study except during the 7 days preceding the start of renal physiology laboratory assessments when they will be instructed to follow a modified diet, refer to G below for details.
- G. Subject will be instructed to adhere to a high-sodium (preferably > 140 mmol/day) and moderate-protein (<1.5g/kg/day) diet during the 7 days preceding the start of renal assessments at baseline during Visits 3 and 4 (the diet to continue until the end of renal assessments at baseline, Visit 4) and during the 7 days preceding the start of the end of treatment renal assessments during Visits 12 and 13 (the diet to continue until the end of renal assessments). The initial 8-point HBGM must be performed prior to start of the modified diet (i.e. prior to day -7). If a subject fails to adhere to the prescribed high-sodium and moderate-protein diet, the investigator will assess whether the subject is still eligible to start the renal assessments based on the subject's actual diet during the 7 days preceding Visit 3. In cases of an unsatisfactory diet, subjects may have to be screen failed based on the investigator's judgement.

Proprietary confidential information.

© 2012 Boehringer Ingelheim International GmbH or one or more of its affiliated companies. All rights reserved.

This document may not - in full or in part - be passed on, reproduced, published or otherwise used without prior written permission.

- H. A local pregnancy test will be done in women of child bearing potential. More frequent testing can be done if required by the local regulation and/or authority or per investigator judgement.

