### Clinical efficacy and safety

More than 190 healthy volunteers were exposed to BI 10773 (dose range: 0.5 mg to 800 mg per single dose and up to 50 mg in multiple dosing). Approximately 170 Caucasian and Japanese subjects with T2DM have been exposed to BI 10773 in phase I studies with a duration of 2-4 weeks and approximately 600 subjects with T2DM have completed up to 12 weeks of treatment with different doses of BI 10773 in two phase II studies; refer to the Investigator's Brochure for additional details.

Increased urinary glucose excretion (UGE) compared with placebo was observed at all doses of BI 10773 in both healthy volunteers and T2DM subjects. The 12-week phase II studies demonstrated an HbA1c reduction of up to 0.72 % (placebo subtracted), a fasting plasma glucose (FPG) reduction of up to 32 mg/dL and a weight loss of approximately 1.5 kg, in both the monotherapy setting and as an add-on to metformin ( $\geq 1500$  mg/day).

Treatment with BI 10773 resulted in a similar percentage of overall Adverse Events (AEs) (approximately 44 %) and Serious Adverse Events (SAEs) (approximately 2%) compared to placebo and/or active comparators. Treatment with BI 10773 showed a higher frequency of genital tract infections and symptoms of pollakiuria/polyuria/nocturia, yet was not associated with a higher incidence of urinary tract infections or hypoglycaemia.

In summary, BI 10773 was well tolerated in Phase I and Phase II studies in healthy male volunteers and subjects with T2DM. The safety profile of BI 10773 was comparable to placebo and there have been no deaths related to BI 10773. The vast majority of AEs considered related to BI 10773 have been of mild to moderate nature. Given the good safety profile in the preclinical studies of BI 10773 at all dose levels and the good tolerability seen in the clinical study program to date, the available clinical and non-clinical data support the further development of BI 10773 in larger studies with long term treatment durations of 26 weeks and above.

For further details refer to the current version of the BI 10773 Investigator's Brochure.

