#### 4.2.2.2 Restrictions on diet and life style

At the beginning of the Run-in period (i.e. at Visit 2), subjects will receive diet and exercise counselling by the Investigator or a member of the clinic staff. The counselling will be based on local diet recommendations for subjects with T1DM in consideration with each subject's possible concomitant illnesses. Site specific tools may be used to help subjects with diet and life style / exercise counselling. The subjects will be reminded to follow the recommended diet and exercise plan during the study. Subject are also requested to adhere to a specific high-sodium (preferably > 140 mmol/day) and moderate-protein (< 1.5 g/kg/day) diet only during the 7 days preceding the start of renal physiology laboratory assessments (respectively 7 days before study Days 1-2 and 57-58). Details of this specific diet will be given to subjects at Visit 2 and subjects will be reminded to re-start this diet at Visit 11.

Women of child-bearing potential must continue to practice an acceptable method of birth control (in accordance with the trial exclusion criteria [Section 3.3.3](#)) throughout the duration of the study including the follow up period.

Subjects should also not take part in another clinical trial involving an investigational medicinal product within the last 30 days before the date of informed consent for this trial.

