##### Other exploratory diabetes mellitus endpoints:

The other exploratory diabetes endpoints include:

- Change from baseline in HbA1c after 8 weeks of treatment with BI 10773
- Change from baseline in ~~glycated albumin (GA)~~ **fructosamine (FA)** after 8 weeks of treatment with BI 10773
- Change in fasting plasma glucose from baseline
- Change in glycaemic exposure, variability and stability as derived from Continuous Glucose Monitoring (CGM) from baseline
- Change in parameters of glucose variability (as measured by CGM or home blood glucose monitoring [HBGM])
- Change in mean daily glucose (as derived from the 8-p HBGM)
- Change in AUC for glucose (CGM data) from baseline
- Change in basal, bolus and total insulin requirement from baseline
- Change in basal insulin requirement day vs night from baseline
- Change in the numbers of bolus boosts from baseline
- Change in UGE from baseline
- Change in BP from baseline
- Change in the Diabetes Treatment Satisfaction Questionnaire from baseline

Proprietary confidential information.

© 2012 Boehringer Ingelheim International GmbH or one or more of its affiliated companies. All rights reserved.

This document may not - in full or in part - be passed on, reproduced, published or otherwise used without prior written permission.

- Change in HbA1c, hypoglycaemia and insulin requirements from baseline (refer to [7.3.2](#) for details of responder classification)

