## 5.2 SAFETY

### 5.2.1 Endpoints of safety

- Incidence of adverse events

Proprietary confidential information.

© 2012 Boehringer Ingelheim International GmbH or one or more of its affiliated companies. All rights reserved.

This document may not - in full or in part - be passed on, reproduced, published or otherwise used without prior written permission.

- Protocol-specified significant adverse events
- Hypoglycaemic events: Occurrence of serious hypoglycaemia, symptomatic hypoglycaemia (mild or moderate) and time spent in CGM defined hypoglycaemia
- Hypoglycaemic events or time spent in CGM-defined hypoglycaemia day vs. night
- Change in frequency of asymptomatic hypoglycaemia <3.0 mmol/l (by home blood glucose monitoring) from baseline
- Change in weight from baseline
- Change in waist circumference
- Changes from baseline in clinical laboratory values (e.g. electrolytes)
- Vital signs

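### Waist circumference has no pre-drug value off the high-sodium diet, so its Visit 8 and Visit 15 changes mix diet with drug; blood pressure and weight are affected only if Visit 3 is their baseline

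*Protocol*

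**What the plan says.** Footnote G of the protocol's Flow Chart tells subjects to "adhere to a high-sodium (preferably > 140 mmol/day) and moderate-protein (<1.5g/kg/day) diet during the 7 days preceding the start of renal assessments at baseline", with "the diet to continue until the end of renal assessments at baseline, Visit 4". The same diet applies in the week before Visits 12 and 13. Section 4.2.2.2 confines it to these two windows and adds that "subjects will be reminded to re-start this diet at Visit 11". Visits 8 and 15 are therefore off the diet. Dosing runs from Day 3 to Visit 13 (Day 58).

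The Flow Chart ticks are:

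- Vital signs: Visits 1, 2, 3, 4, 8, 12, 13, EOT and 15.
- Weight: Visits 1, 3, 8, 12, EOT and 15.
- "Waist circumference": Visits 3, 8, 12, EOT and 15.

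None of the three is ticked at Visit 11 (Day 50). That is an in-person visit, and footnote A states that "Visits 2, 11 and if required EOT are the only clinic visits where a fasting status is required for labs".

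Section 5.1.1 lists "Change in BP from baseline" among the other exploratory diabetes endpoints. Section 5.2.1 lists "Change in waist circumference" and the change in weight among the safety endpoints. Section 7.1 fixes baselines for laboratory, renal and hypoglycaemia measures, but not for blood pressure, weight or waist.

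**The concern.** A prescribed change in sodium intake can shift body fluid, and with it blood pressure, weight and possibly waist. The only waist reading before treatment is taken after a week on that diet, while two of the later readings are taken off it. If the diet raises waist, its disappearance at Visit 8 reads as a loss on the drug. At Visit 15, two weeks after the last dose, it reads as a loss that persists after the drug.

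The protocol guards other measures against this. Footnote G requires the first 8-point glucose profile before the diet starts, and the last on-treatment profile is on Day 49, the day before Visit 11. Fasting glucose and lipids are paired at Visit 2 and Visit 11. Waist has no such pair. Blood pressure and weight lack the late half of it.

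**Working it through.** No sample size or power figure is involved. The check classifies each scheduled reading by drug and diet, using the Flow Chart rows and the diet windows in footnote G and Section 4.2.2.2. EOT readings are left out because they exist only for early discontinuers.

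| Visit (day) | Drug | Diet | BP | Weight | Waist |
|---|---|---|---|---|---|
| 1 (-21) | off | off | yes | yes | no |
| 2 (-14) | off | off | yes | no | no |
| 3 (1) | off | on | yes | yes | yes |
| 4 (2) | off | on | yes | no | no |
| 8 (29) | on | off | yes | yes | yes |
| 11 (50) | on | restarting | no | no | no |
| 12 (57) | on | on | yes | yes | yes |
| 13 (58) | on | on | yes | no | no |
| 15 (72) | off | off | yes | yes | yes |

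Let m be the mean off drug and off diet before treatment. Let S be the effect of the diet, D8 and D12 the drug effects at Visits 8 and 12, and R15 what remains at Visit 15. Assume that the effects add. The waist means are then:

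- Visit 3: m + S
- Visit 8: m + D8
- Visit 12: m + D12 + S
- Visit 15: m + R15

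The changes from Visit 3 are:

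- Visit 8 - Visit 3 = D8 - S (mixed)
- Visit 12 - Visit 3 = D12 (diet-matched)
- Visit 15 - Visit 3 = R15 - S (mixed)

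Four visit means have to supply five unknowns (m, S, D8, D12, R15), so D8, R15 and S cannot be separated. Setting R15 to zero would close the system, but it assumes the answer to the Visit 15 question. Visit 15 is 72 - 58 = 14 days after the last dose. Section 3.2 says that the pharmacodynamic effect lasts about three days, but that does not show that waist has returned to its starting value.

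A waist reading at Visit 2 supplies m directly. There are then five means for five unknowns: Visit 8 - Visit 2 = D8 and Visit 15 - Visit 2 = R15.

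For weight, Visit 1 already supplies m. For blood pressure, Visits 1 and 2 do. Their Visit 8 and Visit 15 changes are mixed only if Visit 3 is chosen as baseline.

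For all three measures, the scheduled on-treatment readings after Visit 8 are at Visit 12 and, for blood pressure, Visit 13. Both visits are on the diet.

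**The case against.** The strongest reply is that the end-of-treatment comparison is already well controlled. Visit 12 against Visit 3, and Visit 13 against Visit 4 for blood pressure, compare like with like, and footnote L checks sodium by 24-hour urine collection before Visits 3 and 12. Usual diet at Visits 2, 8, 11 and 15 has no such check, so preferring it is a choice of question. This stands: the 8-week change is sound, although it describes subjects on the prescribed diet only.

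A second reply is that the choice of baseline for blood pressure and weight is commonly left to the statistical analysis plan, which is not at hand. This also stands, and so those two measures cannot be called confounded. It does not help waist, because no plan can select an off-diet value that was never taken.

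A third is that Visit 11 is not reliably ahead of the diet. It falls on Day 50 ± 2, that is Days 48 to 52. Visit 12 falls on Day 57 ± 4, that is Days 53 to 61, so the diet may begin on Days 46 to 54. The overlap is real, and the fix has to allow for it.

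A reader might also infer a size for the bias by setting retained fluid against "a weight loss of approximately 1.5 kg" in Section 1.2. The documents do not support that. The figure comes from 12-week studies in type 2 diabetes, and nothing in the protocol gives usual sodium intake or the fluid that the diet retains.

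**Conclusion.** The point holds for waist. Its Visit 8 change combines stopping the diet with the drug effect, and its Visit 15 change combines stopping the diet with the post-drug state. In both cases the error is the diet effect S, one for one. The documents give no value for S. It may be near zero if usual sodium intake is already similar to the prescribed level. The algebra assumes additive effects.

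A reader might infer that all three measures are confounded throughout. They are not. The 8-week changes are diet-matched, and blood pressure and weight have off-diet pre-drug values. What is missing for all three is an off-diet reading on treatment after week 4 in completers.

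The point is minor. It touches exploratory and safety endpoints that are summarised descriptively, and leaves the primary GFR analysis as it is.

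**What to change.** In the Flow Chart, add waist and weight at Visit 2, and vital signs, weight and waist at Visit 11. Take the Visit 11 readings before the diet restarts and, because the visit windows allow overlap, record whether it has already begun.

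In Section 7.1, state that changes in these measures at Visits 8, 11 and 15 use the off-diet baseline at Visit 2, and that changes at Visits 12 and 13 use Visits 3 and 4 respectively.

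The cost is a few minutes at two clinic visits that already take place, and a sentence in Section 7.1. No visit or sample is added.

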## ABBREVIATIONS

|                   |                                                |
|-------------------|------------------------------------------------|
| AE                | Adverse Event                                  |
| AGP               | Ambulatory Glucose Profile                     |
| AIx               | Radial augmentation index                      |
| ALT               | Alanine aminotransaminase                      |
| AP                | Alkaline Phosphatase                           |
| AST               | Aspartate aminotransaminase                    |
| AUC               | Area Under the Curve                           |
| BG                | Blood Glucose                                  |
| BI                | Boehringer Ingelheim                           |
| BMI               | Body Mass Index                                |
| BP                | Blood Pressure                                 |
| CGM               | Continuous Glucose Monitoring                  |
| CI                | Confidence Interval                            |
| CML               | Local Clinical Monitor                         |
| CRA               | Clinical Research Associate                    |
| CRF               | Case Report Form                               |
| CSII              | Continuous Subcutaneous Insulin Infusion       |
| CTCAE             | Common Terminology Criteria for Adverse Events |
| CTMF              | Clinical Trial Master File                     |
| CTP               | Clinical Trial Protocol                        |
| CTR               | Clinical Trial Report                          |
| DBP               | Diastolic Blood Pressure                       |
| dL                | Decilitre                                      |
| DMC               | Data-Monitoring Committee                      |
| DTSQ              | Diabetes Treatment Satisfaction Questionnaire  |
| ECG               | Electrocardiogram                              |
| eCRF              | Electronic Case Report Form                    |
| eGFR              | Estimated Glomerular Filtration Rate           |
| EDC               | Electronic Data Capture                        |
| EDTA              | Ethylenediaminetetraacetic acid                |
| EOT               | End Of Treatment                               |
| ERPF              | Effective Renal Plasma Flow                    |
| ESRD              | End Stage Renal Disease                        |
| EudraCT           | European Clinical Trials Database              |
| FA         | Fructosamine                            |
| FAS               | Full Analysis Set                              |
| FF                | Filtration Fraction                            |
| FPG               | Fasting Plasma Glucose                         |
| <del>GA</del>     | <del>Glycated Albumin</del>                    |
| GCP               | Good Clinical Practice                         |
| GFR               | Glomerular Filtration Rate                     |
| GTI               | Genital Tract Infection                        |
| HbA 1c | Hemoglobin A1c (glycated hemoglobin)           |
| HBGM              | Home Blood Glucose Monitoring                  |

Proprietary confidential information.

© 2012 Boehringer Ingelheim International GmbH or one or more of its affiliated companies. All rights reserved.

This document may not - in full or in part - be passed on, reproduced, published or otherwise used without prior written permission.

|           |                                                   |
|-----------|---------------------------------------------------|
| hCG       | Human Chorionic Gonadotropin                      |
| HPLC      | High-Performance Liquid Chromatography            |
| HPC       | Human Pharmacology Centre                         |
| hr        | Hour                                              |
| IB        | Investigator's Brochure                           |
| IEC       | Independent Ethics Committee                      |
| IRB       | Institutional Review Board                        |
| ISF       | Investigator Site File                            |
| IU        | International Unit                                |
| i.v.      | intravenous                                       |
| Kg        | Kilogram                                          |
| LTs       | Liver Transaminases                               |
| m         | Meter                                             |
| MAP       | Mean Arterial Pressure                            |
| MAGE      | Mean Amplitude of Glycaemic Excursions            |
| MDI       | Multiple Daily Injections                         |
| MDG       | Mean Daily Glucose                                |
| MedDRA    | Medical Dictionary for Drug Regulatory Activities |
| mg        | Milligram                                         |
| min       | Minute                                            |
| ml        | Millilitre                                        |
| mmol      | Millimole                                         |
| MS        | Mass Spectrometry                                 |
| MST       | Medical Subteam                                   |
| NO        | Nitric Oxide                                      |
| NOAEL     | No Observed Adverse Effect Level                  |
| OPU       | Operative Unit                                    |
| p.o.      | per os (oral)                                     |
| PAH       | Paraaminohippurate                                |
| PCC       | Protocol Challenge Committee                      |
| PK        | Pharmacokinetic                                   |
| PWV       | Pulse Wave Velocity                               |
| q.d. (QD) | quaque die (once a day)                           |
| RAAS      | Renin-Angiotensin-Aldosterone System              |
| RBF       | Renal Blood Flow                                  |
| RVR       | Renal Vascular Resistance                         |
| SAE       | Serious Adverse Event                             |
| SBP       | Systolic Blood Pressure                           |
| s.c.      | Subcutaneous                                      |
| SD        | Standard Deviation                                |
| SGLT-2    | Sodium-dependent Glucose co-Transporter 2         |
| SLC5      | Sodium-Glucose Co-transport 5                     |
| SNS       | Sympathetic Nervous System                        |
| SOP       | Standard Operating Procedure                      |
| T1DM      | Type 1 Diabetes Mellitus                          |
| T2DM      | Type 2 Diabetes Mellitus                          |

Proprietary confidential information.

© 2012 Boehringer Ingelheim International GmbH or one or more of its affiliated companies. All rights reserved.

This document may not - in full or in part - be passed on, reproduced, published or otherwise used without prior written permission.

|      |                                 |
|------|---------------------------------|
| TCM  | Trial Clinical Monitor          |
| TGF  | Tubuloglomerular Feedback       |
| TSAP | Trial Statistical Analysis Plan |
| TSH  | Thyroid Stimulating Hormone     |
| UGE  | Urinary Glucose Excretion       |
| USA  | United States of America        |
| UTI  | Urinary Tract Infections        |
| V    | Visit                           |
| WHO  | World Health Organization       |

Proprietary confidential information.

© 2012 Boehringer Ingelheim International GmbH or one or more of its affiliated companies. All rights reserved.

This document may not - in full or in part - be passed on, reproduced, published or otherwise used without prior written permission.

